### Hypothesis and objectives

Our previous studies suggest that malnourished women of childbearing age living in Mirpur exhibit small intestinal enteropathy resembling that found in Mirpur children with EED [4–6, 18]. In our current study, we will test the hypothesis that SI microbiota contributes to small intestinal enteropathy and malnutrition in young Bangladeshi women of childbearing age. An interventional component will be included involving the administration of MD-BEP or RUSF-BEP in pregnant and non-pregnant undernourished women. This will be based on the hypothesis that transmission of the microbiota of mothers with EED to their children perpetuates intergenerational undernutrition. The overarching goals for the current study will be to (i) delineate mechanisms by which the SI microbial community obtained from undernourished Mirpur women contributes to maternal malnutrition and identify surrogate biomarkers that can be applied to malnourished pregnant women, and (ii) test whether MD-BEP can ameliorate EED as judged by these surrogate endpoints in undernourished women (who are either pregnant or non-pregnant).

### Methods and analysis

This is a community-based intervention study where participants will be enrolled in two cohorts: undernourished pregnant (BMI < 18.5 kg/m^2^; 18–35 years, *n* = 60) and undernourished non-pregnant ((BMI < 18.5 kg/m^2^; 18–35 years, *n* = 60) women from Bauniabadh and adjacent slum areas of Mirpur, Dhaka. For comparison, well-nourished pregnant women (BMI 20–24.9 kg/m^2^; 18–35 years, *n* = 30), who will be screened through household surveys from the Bauniabadh and adjacent slum area of Mirpur, Dhaka, and well-nourished non-pregnant (BMI 20–24.9 kg/m^2^; 18–35 years, *n* = 30) women of reproductive age will be recruited. We will use two specific aims, AIM 1 A and AIM 1B. In AIM 1 A, we will compare the small intestinal (SI) and fecal microbiota and the plasma, duodenal, and fecal proteomes/metabolomes of the undernourished non-pregnant cohort with histopathologic evidence of EED with the well-nourished non-pregnant cohort with no histopathologic evidence of EED undergoing routine endoscopic evaluation for dyspepsia. Upper gastro-intestinal (UGI) endoscopy will be performed on non-pregnant women and biopsy samples will be collected for diagnosis of EED and histopathological scoring. In AIM 1B, we will perform an intervention study. After UGI endoscopy, undernourished non-pregnant cohort will be randomized into two groups (*n* = 30/arm) and receive daily dietary supplementation with either shelf-stable microbiota-directed balanced energy protein (MD-BEP) or ready-to -use supplementary food balanced energy protein (RUSF-BEP) for 90 days. After cessation of the intervention they will be further followed up for another 270 days and biological samples will be collected at scheduled time points. The well-nourished non-pregnant cohort will not receive any nutritional intervention will serve as a reference control group. The undernourished pregnant cohort will also be randomly (*n* = 30/arm) assigned to receive either MD-BEP or RUSF-BEP daily for 6 months until the child birth and thereafter for 3 months and followed up for another 9 months. During this period anthropometry will be measured and biological samples including fecal and plasma samples will be collected from the mothers and their infants in scheduled time points. The well-nourished pregnant cohort will not be supplemented with MD-BEF or RUSF-BEP but will be followed-up with anthropometric measurement and sample collection like undernourished pregnant cohort. Due to ethical concerns related to performing endoscopy in pregnant women, UGI endoscopy in pregnant women will not be performed. Anthropometric, socio-demographic, and laboratory assay data will be compared across study groups. Additionally, potential EED biomarkers will be evaluated for correlations with nutritional status and histopathological findings, alongside analyses of the microbial community structure. Prior to participation, each subject will receive a comprehensive explanation of the study and provide written informed consent. Participants capable of signing will do so, while those unable to sign will provide a thumb impression as an alternative. A separate consent form specific to endoscopy and supplemental interventions will be administered, following the same consent procedure. The endoscopy consent form thoroughly details all aspects of the procedure, including associated risks, ensuring complete transparency. No information pertinent to the participant’s understanding is withheld. While enrolling the neonates, a signed written informed consent from the parents or guardians is obtained. All consents are obtained and documented in presence of the study physician at the study field office in front of a witness, who also sign the document as the witness. This study was conducted and reported in accordance with the CONSORT guidelines. The first participant was enrolled on 28 April 2023. Estimated end date is 31 December 2026. The schedule of study events is presented in Fig. 1.

**Fig. 1 Fig1:**
[figure not shown]
Schedule of study events

### AIM 1A: non-pregnant cohort

In AIM 1 A, for the healthy group, we plan to recruit a cohort of well-nourished Bangladeshi women who will undergo esophagogastroduodenoscopy (EGD) for evaluation of functional dyspepsia and identify 30 well-nourished participants who have normal duodenal mucosal histology. Healthy women (BMI 20–24.9 kg/m^2^) of childbearing age who have been referred for evaluation of functional dyspepsia as defined by Rome IV criteria, will be enrolled from women attending the Gastroenterology OPD of Bangladesh Specialized Hospital (BSH), Dhaka, Bangladesh, and also from the community who meet the inclusion criteria. Duodenal biopsies, duodenal aspirates, plasma and fecal specimens from these participants at the time of endoscopy and serial plasma and fecal samples will be collected according to the follow-up schedule (Fig. 3). These women will be considered as the control group for the non-pregnant cohort and will be followed for 360 days but will not receive any nutritional intervention. Undernourished (< 18.5 kg/m^2^; 18–35 years) women of childbearing age will be enrolled from Bauniabadh and adjacent slum areas of Mirpur, Dhaka, and EGD will be performed among 60 women at icddr, b Dhaka Hospital, or BSH, Dhaka. Participants will be screened through household surveys from the Bauniabadh and adjacent slum area of Mirpur, Dhaka. After EGD, the undernourished women will be randomized into two groups (*n* = 30/arm) and receive daily dietary supplementation with either MD-BEP or RUSF-BEP for a period of 90 days, with a further 270 days of follow-up after cessation of the intervention, and biological samples will be collected from the participants according to the schedule. The EGD scheme is presented in Fig. 2.

**Fig. 2 Fig2:**
[figure not shown]
Intervention, sample (plasma, feces, intestinal biopsy and aspirate) collection and follow-up scheme for AIM 1A

### AIM 1B: pregnant cohort

For AIM 1B, beginning at the end of the first trimester, undernourished (< 18.5 kg/m^2^) pregnant women (aged 18–35 years) will be randomly assigned to receive either MD-BEP or RUSF-BEP for the duration of their pregnancy and during the first three postnatal months, in addition to standard antenatal care (*n* = 30/arm). A parallel cohort of age-matched well-nourished pregnant women (*n* = 30) who will not receive any nutritional intervention will serve as a reference control group. Due to safety, sensitivity, and ethical concerns related to performing endoscopy in pregnant women, EGD will not be performed on these women. The women will receive standard antenatal care, will be followed up and serial plasma and fecal samples will be collected according to Fig. 1. These women will be considered as the control group for the pregnant cohort and will not receive any nutritional intervention.

**Fig. 3 Fig3:**
[figure not shown]
Intervention, sample (plasma, feces, intestinal biopsy and aspirate) collection and follow-up scheme for AIM 1B

### EGD and biopsy sample collection

Endoscopy will be performed at icddr, b Dhaka Hospital and Bangladesh Specialized Hospital (BSH). Clinical metadata will be collected, including socio-demographic data, dietary history, and use of antibiotics and proton pump inhibitors (PPI) during 12 months prior to EGD. EGD will be performed according to standards recommended by the American College of Gastroenterology (ACG) and the American Society for Gastrointestinal Endoscopy (ASGE) [16]. The endoscopist will use sterile ERCP catheters to collect secretions from the second part of the duodenum (prior to biopsy). Aspirates (~ 1–2 mL/subject) will be divided into aliquots and stored in a manner that preserves bacterial viability using the protocol we employed in the BEED study for children with EED [4].

### Histopathology definition of EED

After EGD, histopathology will be performed to identify women who have EED. An operational categorization of EED used previously based on three histopathologic features (presence of inflammatory cell infiltration in the lamina propria, shortening or loss of small intestinal villi, and increased size or proliferation of the crypts of Lieberkuhn) evident in hematoxylin- and eosin-stained tissue sections will be employed [17]. Histopathologic and immunocytochemical analyses will be conducted at BSH. The biopsies will also be processed at BSH and the standard operating procedure used at BSH will be followed. The scoring systems developed by *Liu et al.* and the categorization of intestinal histomorphology by *Hossain et al.* will be used for the H&E sections [5, 6, 17]. Since inflammatory infiltration typically precedes structural changes like villus atrophy or crypt hyperplasia:

Grade 0 (No EED): No inflammatory infiltration or structural changes.Grade 1 (Mild EED): Inflammatory infiltration in the lamina propria only.Grade 2 (Moderate EED): Inflammatory infiltration with either villous blunting/atrophy or crypt hyperplasia.Grade 3 (Severe EED): Inflammatory infiltration with both villous and crypt abnormalities.

### Processing of collected biological samples

Schedule for biological sample collection is indicated in Figs. 1 and 2. All biological samples (blood and stool) will be collected in accordance with the standard operating procedures (SOPs) outlined for this protocol. A total of 5 ml of blood will be drawn from each participant. Collected fecal samples will be cryopreserved within 20 min after defecation. At the collection location, the samples will be divided into sterile, pre-labelled 2 mL cryovials and promptly transferred into pre-cooled liquid nitrogen dry shippers for transportation to the laboratory. At the laboratory, vials will be transferred from the dry shipper to a bucket of dry ice which is used during the organization and transfer of samples into 9 × 9 freezer boxes. and immediately placed into a −80 °C freezer. No additives, preservatives or media will be added to the fecal samples. The preparation and transport of all biological samples will strictly adhere to the biosafety laws and procedures of both institution’s and international standards. An aliquot of each fecal sample will be used at icddr, b for (i) Taqman Array Card (TAC)-based assays of 34 enteropathogens and (ii) commonly used clinical markers of intestinal inflammation and barrier disruption [ELISA of several fecal (and plasma) biomarkers including CRP, AGP, myeloperoxidase, neopterin, alpha-1 anti-trypsin, calprotectin, Reg1B, lipocalin-2 (LCN2), and Duox-2].

### Details of intervention products

#### Microbiota directed- balanced energy protein (MD-BEP)

Every woman in the MD-BEP arm will be offered a single serving of MD-BEP daily, aimed as a supplement to the usual diet received by these women. The feeding will initially take place in the field office under direct supervision for at least one week, and continued at home afterwards. The feeding will be supervised by the respective field research assistants (FRAs) in regular intervals at home. MD-BEP will provide approximately 500 Kcal, 14 g of protein and the necessary micronutrients, and the substrate for the beneficial microbiota proliferation.

#### Ready-to-use supplementary food- balanced energy protein (RUSF-BEP)

Women in the RUSF-BEP group will receive a single serving of RUSF-BEP daily, similar to the MD-BEP arm. The feeding will initially in the field office for at least one week, and continued at home afterwards. The feeding will be supervised by the respective FRAs. Each serving of RUSF-BEP will also provide approximately 500 Kcal, 14 g of protein, and necessary micronutrients following the recommendations from the expert panel convened by the BMGF on nutritional supplementation in pregnancy [15].

The amount in each serving of the supplements and the compositions are shown in Tables 1 and 2, respectively, which are in conformity with the recommendations from the expert panel convened by the BMGF on nutritional supplementation in pregnancy [15].

**Table 1 Tab1:** Ingredients used in MD-BEP and RUSF-BEP formulations with amount per serving

Ingredients	MD-BEP (gms)	RUSF-BEP (gms)
Chickpea, flour	14.00	-
Soy flour	18.50	-
Peanut, paste	14.25	-
Green banana powder	12.50	-
Sugar, powder	11.90	10.30
Soybean Oil	20.00	28.50
Micronutrient Premix	2.30	2.30
Amino acid powder (Lysine 0.15, Methionine 0.05, Cysteine 0.05)	0.25	-
Stabilizers (Lecithin)	0.30	0.30
Rice, flour	-	13.40
Lentil, flour	-	14.60
Skimmed Milk, Powder	-	27.60
Total	94	97

Enrolled women will be closely monitored by Field Research Assistants for one week to identify any potential side effects or adverse events (e.g., rash, urticaria due to food allergy, or notable changes in clinical status). Any such events will be managed in accordance with the standard of care. Study participants will be given dietary counseling focused on promoting dietary diversity, incorporating vegetable oil into cooked meals as an energy source, and encouraging regular consumption of animal-based foods such as small fish or chicken, alongside a consistent intake of vegetables. The study participants will also receive support for any intercurrent illnesses detected by the study team as well as proper referral will be provided.

**Table 2 Tab2:** Nutritional composition of MD-BEP and RUSF-BEP

Nutritional composition	BEP recommendation	MD-BEP (per 94 g)	RUSF-BEP (per 97 g)
Total Energy(kcal)	250–500	494.62	497.54
Protein (g)	14–18	14.18	14.33
Energy from Added Sugar, (% of total energy)	< 10%	9.36%	8.05%
Energy from Fat (FER), (% of total energy)	10–60%	58.48%	53.08%
Total ω−3 (g)	≥ 1.30	1.70	2.01
(ω−6/ω−3) ratio	5–10:1	8.29:1	7.34:1
Total Trans-fatty acid (g)	< 1.00	0.16	0.19
DIAAS	≥ 90%	91.67%	123.64%

#### Manufacturing of intervention products

The servings will be provided in sterilized formulations packaged in trilaminar foil pouches developed in Natore Agro Limited (NAL) factory, a sister concern of a renowned food manufacturing company of Bangladesh, PRAN. A standardized production process will be followed to maintain the quality of the formulations throughout the project period. All raw materials will first undergo a rigorous quality control process. The selected ingredients will then be roasted in a temperature-controlled hot air oven and ground into a fine powder or paste using a heavy-duty electric grinder, as appropriate. The mixture will be portioned into trilaminar foil pouches, with each processing step closely monitored. Pouches will be sealed using an impulse sealer to ensure airtight packaging, followed by sterilization in a retort machine at 105 °C and 0.123 MPa for 10 min. This sterilization protocol is designed to extend shelf life and maintain the food’s organoleptic qualities. Prior to finalization, supplement prototypes will be assessed for microbiological safety and sensory acceptability. Additionally, during manufacturing and distribution, random samples from each batch will be tested for microbial contamination and organoleptic characteristics.

### Data collection

At study initiation, data on demographic characteristics—such as household wealth, husband’s occupation and income, housing conditions, family structure, and home environment—will be collected. Morbidity information will be gathered on a weekly basis throughout the intervention period.

### Anthropometry and body composition

Nutritional status will be assessed through anthropometry. Body weight and BMI will be determined at the anthropometry timepoints mentioned in Figs. 2 and 3. Bioelectric Impedance Analysis (BIA) will be used to measure total fat and fat-free mass before, during and after the intervention.

### Follow-up of pregnant women

Pregnant women will be enrolled at the beginning of second trimester and followed up till one year after childbirth. For the undernourished pregnant women, antenatal care (ANC) services from nearby healthcare facilities will be ensured by study staff. Trained Health Workers (HWs) will visit the homes of all enrolled pregnant women once a month and will involve the family members, including mothers, mothers-in-law, and husbands, along with the pregnant women in the sessions according to the convenience and availability of the participant and her family members. The woman and her family will receive advice on the importance of adequate weight gain during pregnancy, additional energy requirements, and improving dietary diversity. The pregnant women will be advised to seek routine ANC according to the schedule and to regularly take micronutrients (iron, folic acid, and calcium) provided through routine ANC. On each visit, the participants’ dietary diversity and rate of weight gain will be evaluated, and they will be given instant feedback. The participants will have access to field offices where they shall receive a thorough physical check-up by a registered physician. If any unwanted event occurs during the follow-up period, the participants will be referred to the nearest maternal clinic or appropriate healthcare facility.

### Available health care services for low-BMI pregnant women in the study site

The Bauniabadh area of Dhaka city is located in ward-5 of Dhaka North City Corporation [3, 18, 19]. The accessibility of various facilities and services for secondary and tertiary healthcare has increased significantly. Medical clinics and diagnostic centers are now widely available across the region. Medical clinics and diagnostic centers have become numerous all over the area outside slums. In this area, health infrastructure facilities, managed and operated by various organizations, can be classified into three categories: (i) public, (ii) private, and (iii) non-governmental organizations (NGOs). Currently, in this particular area, primary health care targeting maternal and child nutrition is provided by The Asian Development Bank (ADB)-supported Urban Primary Health Care Project (UPHCP II) and the USAID-supported NGO Services Delivery Program, which served as a precursor to the current Smiling Sun Franchise Program (SSFP), Urban Health Center by BRAC, and Radda MCH-FP center. The services provided by these facilities include basic medical consultation, diagnostics, EPI, pregnancy and delivery services, including ANC, Infant and Young Child Feeding (IYCF) services, and nutrition counseling.

### Sample size calculation and outcome

For normal-BMI (BMI 20–24.9 kg/m^2^) women of childbearing age or healthy volunteers undergoing EGD, the goal is to identify 30 normal-BMI participants who will undergo EGD for evaluation of functional dyspepsia and will have normal duodenal mucosal histology. We plan to recruit 100 individuals for EGD, and anticipate that 60 will have duodenal mucosa without macroscopic evidence of active acid-peptic disease, of whom 30 will have normal duodenal mucosal histology. These calculations are based on the team’s gastroenterologist who has 15-year experience with > 30,000 subjects from this socioeconomic group and geographic locale. These specimens from normal BMI participants without enteropathy will be compared with those of 60 undernourished low-BMI (< 18.5 kg/m2) women of childbearing age. As this is an experimental study, no formal power calculation has been performed for this exploratory research study. The same applies for the pregnant cohort.

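### The expected control yield sheds women with active acid-peptic disease, the undernourished counts show no matching step, and peptic inflammation could therefore contribute to the Aim 1A differences

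*Protocol article*

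**What the plan says.** **Controls.** The section on sample size and outcome states "We plan to recruit 100 individuals for EGD". Of these, the investigators "anticipate that 60 will have duodenal mucosa without macroscopic evidence of active acid-peptic disease, of whom 30 will have normal duodenal mucosal histology". The expectation rests on a gastroenterologist's experience with patients "from this socioeconomic group and geographic locale". The section on Aim 1A gives the goal as to "identify 30 well-nourished participants who have normal duodenal mucosal histology". These women come to endoscopy for functional dyspepsia.

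**Undernourished women.** The section on Aim 1A finds them by household survey and states that "EGD will be performed among 60 women at icddr, b Dhaka Hospital, or BSH, Dhaka". It continues: "After EGD, the undernourished women will be randomized into two groups", with 30 per arm.

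**The comparison.** The abstract and the Methods and analysis section limit the Aim 1A cases to undernourished women with histologic EED. The sample size section refers to all 60: "These specimens from normal BMI participants without enteropathy will be compared with those of 60 undernourished low-BMI" women. Neither mentions acid-peptic disease on the case side.

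**The grading.** In the section on the histopathology definition of EED, Grade 1 is "Inflammatory infiltration in the lamina propria only". The grades as printed do not ask for another cause of infiltration to be ruled out.

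**The concern.** The two groups in Aim 1A appear to reach the comparison by different routes through the same endoscopy. A well-nourished woman with visible acid-peptic disease is expected to drop out before her histology matters. An undernourished woman with the same finding has no stated point at which she would drop out. If her biopsy shows infiltration, she meets the case definition.

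The duodenal microbiota, the duodenal proteome and the inflammation markers could then differ between groups partly because of acid-peptic disease. The consequence reaches beyond Aim 1A. The stated goals are to identify surrogate markers in the women who have endoscopy and to use them to judge the supplement in pregnant women, who will have none. A marker of peptic inflammation taken for an EED marker would go into a cohort with no histology to reveal the mistake.

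**Working it through.** **1. The plan's own figure.** Control yield: 100 × 60/100 × 30/60 = 30. This reproduces the stated 30. The macroscopic step accounts for 100 − 60 = 40 women, and the histology step for 60 − 30 = 30.

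**2. The same account for the undernourished women.** 60 endoscoped, 2 × 30 = 60 randomised, so 0 are shown as lost at endoscopy.

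**3. How many cases could be affected.** Let q be the share of the 60 undernourished women with macroscopic active acid-peptic disease. The article does not give q. I take 0 to 40%. The top is the control figure (40 of 100), which comes from dyspepsia endoscopies and may be too high for women found by household survey. To size the EED group I assume that every affected woman is graded EED, and that 90% of the others are. The 90% is the enteropathy rate that the Introduction reports for malnourished women in the earlier study.

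- Affected = 60q
- EED among the unaffected = 0.9 × 60(1 − q)
- Affected share of EED cases = 60q / [60q + 54(1 − q)]

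| q (assumed) | Affected of 60 | Unaffected EED cases | Affected share of EED cases |
|---|---|---|---|
| 0% | 0 | 54.0 | 0% |
| 10% | 6 | 48.6 | 11% |
| 20% | 12 | 43.2 | 22% |
| 30% | 18 | 37.8 | 32% |
| 40% | 24 | 32.4 | 43% |

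The shares are upper values for each q, because not every affected woman need show infiltration.

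**4. What this could do to a single marker.** This is an illustration, not an estimate. Suppose EED has no effect and a marker is shifted by d standard deviations in affected women only. Compare 30 controls with all 60 undernourished women at two-sided 0.05 (the article gives 0.05 without sidedness). The mean difference is qd. The SD is √(1 + q(1 − q)d²), used for both groups. The chance of rejecting in the direction of the shift is Φ(qd / [SD × √(1/30 + 1/60)] − 1.96), against a nominal 2.5%.

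| q | d = 0.5 | d = 1 |
|---|---|---|
| 10% | 4.1% | 6.3% |
| 20% | 6.4% | 12.9% |
| 30% | 9.6% | 23.0% |
| 40% | 13.8% | 36.2% |

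Worked line for q = 40%, d = 1: SD = √1.24 = 1.114; 0.4 / (1.114 × 0.2236) = 1.606; Φ(1.606 − 1.96) = 36.2%.

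**5. Precision lost by leaving affected women out.** The standard error is proportional to √(1/30 + 1/n), where n is the number of EED cases.

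- q = 10%: n falls from 54.6 to 48.6; 0.2322 / 0.2273 = 1.02.
- q = 40%: n falls from 56.4 to 32.4; 0.2534 / 0.2260 = 1.12.

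The standard error grows by about 2% to 12%.

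**The case against.** Several points on the other side stand.

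- **The macroscopic step is a forecast.** A reader might infer that controls are accepted only if endoscopy shows no active acid-peptic disease. The article gives this as an anticipated yield, and the only stated requirement is normal histology. That requirement would itself remove a control with inflamed mucosa, so the contrast does not depend on the macroscopic step alone.
- **Cases are selected too.** A reader might infer that the undernourished women pass no filter at all. For Aim 1A, the abstract and the Methods and analysis section restrict cases to women with histologic EED. That filter keeps infiltration of any origin, however, so it does not remove the problem.
- **The article is condensed.** It refers to inclusion criteria without listing them, so the full protocol may hold an exclusion. The target of 60 could also be met by replacing women. The article mentions no replacement.
- **The recruitment routes differ.** Acid-peptic findings are to be expected in dyspepsia referrals and may be less common in women surveyed at home. This is why the range starts at 0.
- **The mechanism is not in the documents.** The article does not say that acid-peptic disease leaves infiltration in the biopsied duodenum, and the cited scoring systems, which may separate the two, are not shown.

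A general reply is that confounders will be examined and that use of antibiotics and proton pump inhibitors is recorded. The article ties neither to acid-peptic disease in Aim 1A. Covariate adjustment would also not be enough if no control is affected, because the groups would not overlap on that variable.

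**Conclusion.** The concern holds as a possible contribution to bias in Aim 1A. The article's counts run 100 to 60 to 30 for controls and 60 to 60 for undernourished women, and its case definition does not distinguish the cause of infiltration. Acid-peptic inflammation could therefore be present in the cases and largely absent from the controls.

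Its size cannot be fixed from the document. With an assumed frequency of 0-40%, 0 to 24 of the 60 women are affected. The top of that range requires the dyspepsia-referral rate to apply to women surveyed at home. A reader might go further and conclude that peptic disease drives the Aim 1A differences. The document does not support that, because neither the frequency in undernourished women nor the effect on the markers is given.

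The randomised comparison of the two supplements is not affected, since assignment follows endoscopy and any affected women are allocated by chance. The study's exploratory label explains the lack of a power calculation but does not remove a difference in how the two groups are selected.

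**What to change.** Record macroscopic active acid-peptic findings in the same way, on the same form, at the planned endoscopy in both groups. State in the article or analysis plan whether the macroscopic step is a criterion for controls or only an expected loss.

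Report the Aim 1A comparison and the biomarker correlations twice: in all EED cases, and again excluding women with such findings. Treat as candidate surrogates for the pregnant cohort only markers that hold in both. Define beforehand what it means to hold, preferably by the direction and size of the estimate, because significance alone would penalise the smaller set for its lost precision. Keep all 60 women in the randomised comparison.

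No procedure is added, as every woman concerned already has the endoscopy. The cost is one recorded item, a little extra analysis, and a standard error about 2% to 12% larger in the restricted set if 10% to 40% of the undernourished women are affected. Reporting both sets avoids making the smaller one the sole main analysis, which could give up as many as 24 of the 60 women.
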